**Fig. 1 Fig1:**
[figure not shown]
Flowchart of the Delphi study and nested randomised controlled trial

We will collect demographic information from participants that will be stored in a separate database and used to provide the participant with a unique identifier. Participants will be asked to provide information on their age, background, years of experience, field of interest, working country and current position, to help to define the composition of the panel.

### Randomisation

After round 1, participants will be randomised to one of three groups that will determine the method of feedback they will receive. Participants will be stratified by type of stakeholder to ensure equal representation in each study group. The randomisation process will be conducted through the COMET e-management system.

Study groups are as follows: group 1 will be shown collated responses of the entire panel for each outcome (heterogeneous group); group 2 will be shown collated responses for each outcome only from the stakeholder group to which they belong (homogeneous group); and group 3 will be shown collated responses for each outcome for each stakeholder group (diverse group).

### Rounds 2 and 3

In rounds 2 and 3, all three study groups will receive the same list of outcomes with feedback tailored in accordance with their randomisation. Participants will be asked to reflect on their own response and the collated responses, and score the outcomes again.

### Analysis

During rounds, scores (1–9) will be calculated as a percentage of the total responses. The final responses will be analysed for each of the three study groups. We will define consensus for outcome inclusion in the COS as >70% of responses rating the outcome at 7 or greater and not more than 15% of responses rating the outcome <3 [14]. We will explore similarities and differences across the three COS generated by the different feedback methods. As there is no gold standard for feedback, all three COS will be brought forward to the consensus meeting for consideration and discussion, and for the preparation of a final COS.

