### Panel size and recruitment

There are no generally accepted guidelines for optimal panel size to achieve stable consensus in Delphi studies [13]. Panel size in other projects has usually been guided by practicality, question scope and time available for analysis [11]. We will attempt to recruit as large a panel as possible, and will encourage all organisations within each stakeholder group to nominate between five and ten representatives who meet the inclusion criteria.

Organisations within each stakeholder group will be identified through our wide network of critical care contacts and through a methodological web-based search. We will email study information to key contacts (for example, Chair, President, Director) within organisations, inviting them to nominate expert participants or to forward a recruitment letter.

The French Cochrane Centre will undertake a systematic search of PubMed to identify trial investigators. This search will include appropriate terms for: population (adult and child); interventions (aimed at reducing duration of mechanical ventilation); year of publication (2004–2014); and study type (randomised trials, observational studies). We anticipate an overlap between eligible participants identified through the PubMed search and those identified by CTGs; therefore, we will only recruit those participants not identified by the CTGs into the trial investigator arm.

Previous studies of the Delphi technique demonstrate high attrition after four rounds [10]. Therefore, we will use three rounds and provide two-weekly reminders to participants. Other techniques to minimise attrition include: provision of a personalised invitation and reminders; an outline of timelines; and ensuring that each round is concise and easy to complete with minimal time commitment. Participants will receive an email comprising a clear study explanation emphasising the importance of completing all rounds, an estimate of the amount of time to complete the questionnaires and requesting consent for participation.

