### Ethical requirements

Individual participants will be approached (or will self-volunteer) after nomination by an organisational lead from an organisation with which they are affiliated. Participants will be sent a short introductory email with an information sheet about the study, including details of randomisation, explicit details about what will be involved and asked for their consent to participate. Participants will be given the option to withdraw from the study at any time. This study will be conducted entirely online and consistent with standard practice in survey research; consent will be assumed by agreement to participate and completion of online questionnaires. The study was reviewed and approved by the School of Medicine, Dentistry and Biomedical Science Research Ethics Committee at Queen’s University Belfast (QUB), Northern Ireland, UK, in October 2014 [Ref: 14.34v2] (Ethics Committee Reference). Sponsorship and indemnity is provided by QUB.

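### Analysing only the final responses by arm can mix who stayed with what feedback did, for outcomes near the consensus cuts

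*Protocol article*

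**What the plan says.** All references are to the protocol article.

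- **Timing (Randomisation).** "After round 1, participants will be randomised to one of three groups that will determine the method of feedback they will receive". Allocation is stratified by stakeholder type. One arm sees the collated scores of the whole panel, one sees those of its own stakeholder group only, and one sees those of each stakeholder group separately.
- **Later rounds (Rounds 2 and 3).** All arms score the same list again, with "feedback tailored in accordance with their randomisation".
- **Data analysed (Analysis, Delphi study).** "During rounds, scores (1–9) will be calculated as a percentage of the total responses", and then "The final responses will be analysed for each of the three study groups".
- **Consensus rule (same section).** An outcome qualifies with ">70% of responses rating the outcome at 7 or greater and not more than 15% of responses rating the outcome <3". The denominator is responses. The three resulting COS are compared descriptively and taken to a consensus meeting.
- **Attrition (Panel size and recruitment).** "Previous studies of the Delphi technique demonstrate high attrition after four rounds". "Therefore, we will use three rounds and provide two-weekly reminders to participants". Personalised contact, stated timelines and short questionnaires are also planned. No expected loss is given.
- **Withdrawal (Ethical requirements).** "Participants will be given the option to withdraw from the study at any time".
- **Round 1 scores (Round 1).** Participants score a list of outcomes drawn from the review and may suggest others, which enter at round 2.

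**The concern.** The nested trial exists to show how the feedback method influences ranking, which is the second research question. Randomisation makes the three arms comparable at the point of allocation. If the analysed set is whoever returned round 3, comparability also requires that staying to round 3 does not depend jointly on arm and opinion.

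That condition could fail. The arms differ in how visible disagreement is. A participant who is at odds with the whole panel but in line with their own stakeholder group sees a minority position in the whole-panel arm and not in the own-group arm. If seeing oneself in the minority makes leaving more likely, the feedback changes who is counted as well as what they think.

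Two things are at stake. An outcome may cross a cut in one arm because people left and not because opinion moved. A difference between the three COS may then be credited to the feedback method when part of it reflects retention.

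**Working it through.** The article gives no panel size, power or attrition rate for the Delphi trial, so there is no stated figure to reproduce. The check is arithmetic on the stated rule over assumed rates.

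**Inputs.** From the article: the 70% cut, the 15% limit, and responses as the denominator. Assumed: *s*, the share of those randomised to an arm who would score the outcome 7 or more; *r1*, the share of these who return round 3; *r0*, the share of the rest who return it. Nobody changes their mind.

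**1. Observed support among those who return**

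observed = s·r1 / [s·r1 + (1 − s)·r0], with s = 0.65:

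| r1 v r0 | Calculation | Observed | Above 70%? |
|---|---|---|---|
| equal | any common rate cancels | 65.0% | no |
| 80% v 70% | 0.520 / (0.520 + 0.245) | 68.0% | no |
| 80% v 60% | 0.520 / (0.520 + 0.210) | 71.2% | yes |
| 85% v 55% | 0.5525 / (0.5525 + 0.1925) | 74.2% | yes |

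Overall retention in the 80% v 60% case is 0.52 + 0.21 = 73%. Reversing that case (60% v 80%) gives 0.39 / (0.39 + 0.28) = 58.2%, so the bias can run either way.

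**2. How much selective loss reaches the cut**

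If all supporters stay, the cut is reached when the dropout among the others is f = 1 − (s × 0.3/0.7)/(1 − s). Overall attrition is then f(1 − s).

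| True support | Dropout among the others | Overall attrition |
|---|---|---|
| 68% | 8.9% | 2.9% |
| 65% | 20.4% | 7.1% |
| 60% | 35.7% | 14.3% |
| 55% | 47.6% | 21.4% |

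In whole numbers, with 65 supporters among 100 randomised to an arm, losing 8 of the 35 others gives 65/92 = 70.7%. The effect needs little loss close to the cut and a great deal further away.

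**3. The 15% limit**

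With a true 18% scoring below 3, and loss only among them, the limit is reached at 1 − (0.15 × 0.82/0.85)/0.18 = 19.6% dropout.

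**4. Two arms with the same opinion and the same total attrition**

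Fix s = 0.65 and 20% overall attrition, and let the others drop out at k times the supporters' rate. Supporters' dropout is 0.20/(0.65 + 0.35k), and observed support is 0.65 × (1 − that dropout)/0.80.

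| k | Supporters' dropout | Observed support |
|---|---|---|
| 1 | 20.0% | 65.0% |
| 1.5 | 17.0% | 67.4% |
| 2 | 14.8% | 69.2% |
| 3 | 11.8% | 71.7% |

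An arm at k = 1 and an arm at k = 3 would disagree on this outcome although their members hold identical views and equal numbers left. Similar total attrition across arms is therefore no reassurance; the opinions of those who left have to be examined.

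**The case against.** The strongest case against has five parts.

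- **The text does not expressly exclude anyone.** A reader might infer that the article restricts the analysis to completers. It does not name round 3 as the analysis set, and it does not rule out a participant's last available score. This stands as a limit. Even so, the Analysis section contrasts scores during rounds with final responses, and participants score again in round 3, so round 3 returns remain the natural reading.
- **Missing-data detail belongs in an analysis plan.** It commonly does, and its absence from a condensed article is no fault. The point rests only on what the article fixes: the data analysed and the denominator of the rule.
- **Selective loss is assumed.** This stands. Nothing in the article says that dissenters leave, and individual feedback is anonymised. Dropout is per participant while dissent is per outcome, so one person will usually be in the majority on some outcomes and the minority on others. A 20-point retention gap tied to one outcome is a strong assumption, and the milder 80% v 70% case does not cross the cut.
- **The attrition remark is about four rounds.** A reader might infer that the authors forecast heavy loss here. They cite it as the reason for using three rounds and give no forecast for this study.
- **The consensus meeting intervenes.** A reader might infer that dropout alone could put an outcome into the final COS. It could put it only into one arm's proposal, which the research team and then the meeting consider. This stands for the COS. It does not help the comparison of feedback methods, because nothing stated would show the meeting that an outcome passed through loss of respondents.

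**Conclusion.** The point holds as a conditional one. On the natural reading, the comparison of feedback methods and the consensus rule both condition on an event after randomisation that feedback could affect, and scores collected before randomisation are left unused. If retention depends on opinion, and does so differently by arm, outcomes near the 70% or 15% cuts can change status in an arm's proposed COS without any change of view.

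The percentages rest on assumed support and retention and on nobody changing their mind. They show what the rule can do, not what will happen. Equal retention of supporters and others produces no bias. The comparison of arms is also described as exploratory, with no test or effect estimate stated, which limits the claim without removing it. The documents do not support saying that the comparison will be biased, or in which direction. This is an improvement worth making before the data arrive.

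**What to change.** 1. State that final responses means round 3 returns, and keep that result.
2. For outcomes on the round 1 list, add a comparison of arms on round 2 and round 3 scores, adjusted for round 1 score and stakeholder group. Describe it as covering participants with at least one post-randomisation round. It does not cover everyone randomised, since those who leave before round 2 contribute no outcome.
3. For outcomes added after round 1, which have no round 1 score, adjust for stakeholder group only.
4. Tabulate retention by arm and stakeholder group, and the round 1 scores of completers and non-completers by arm.
5. Repeat the consensus rule with last available scores (round 2, else round 1 where it exists), as a sensitivity analysis only. Flag to the consensus meeting any outcome whose status changes.

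**Cost.** Some wording and a little more analysis. No new data are needed, because the e-management system already collects each round's scores. The Study status section says the Delphi has not begun, so all of this can be set in advance. The real drawback is in step 5. Round 1 scores precede any arm-specific feedback, so carrying them forward pulls the arms towards no difference on the very question being asked. That result must sit beside the completer result and not replace it.

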## Abstract

**Background:**

Among clinical trials of interventions that aim to modify time spent on mechanical ventilation for critically ill patients there is considerable inconsistency in chosen outcomes and how they are measured. The Core Outcomes in Ventilation Trials (COVenT) study aims to develop a set of core outcomes for use in future ventilation trials in mechanically ventilated adults and children.

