### The Delphi panel

A range of expertise within the panel is considered to be an important quality criterion for development of COS [11]. We will therefore seek to include representatives from seven key stakeholder groups that may be particularly interested in this COS. The groups and inclusion criteria are as follows:Industry and pharmaceutical representatives – from companies producing technology and products used in mechanical ventilation.Nurses and allied health professionals (NAHP) – members of professional societies or associations who have a primary role in clinical critical care practice with a minimum of 5 years’ experience.Physicians – members of professional societies or associations who are consultant grade (or equivalent) in intensive care, pulmonology or anaesthetics, and have a primary role in clinical practice.Research funding organisations – representatives from funding bodies that have funded or commissioned critical care research projects in the last 5 years.Patient support groups or charities – representatives from respiratory or critical care charities; patient or relatives user groups, forums or support groups, preferably with personal experience of critical care.Clinical trial groups (CTGs) – members of CTGs that may include the Chair and other appropriate members, preferably representing diverse professions.Trial investigators – primary and senior authors of reports of clinical trials evaluating interventions aiming to reduce duration of mechanical ventilation. These will be identified from a systematic search of publications in PubMed over the last 10 years.

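### The core outcome set is meant for adults and children, but consensus is judged on adult and paediatric responses together, and no described step looks at paediatric responses separately

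*Protocol article*

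**What the plan says.** The Abstract states the aim: to "develop a set of core outcomes for use in future ventilation trials in mechanically ventilated adults and children". Under Panel size and recruitment, the search for trial investigators covers both populations ("population (adult and child").

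The Delphi Analysis section fixes the rule. An outcome must satisfy "We will define consensus for outcome inclusion in the COS as >70% of responses rating the outcome at 7 or greater" and also "not more than 15% of responses rating the outcome <3". The denominator is every response: "scores (1–9) will be calculated as a percentage of the total responses". The one split of the final data that is described is by feedback arm: "The final responses will be analysed for each of the three study groups".

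On the panel, the article says "We will therefore seek to include representatives from seven key stakeholder groups that may be particularly interested in this COS". None of the seven is defined as adult or paediatric. Randomisation is stratified by stakeholder type alone, and the feedback shown is for the whole panel, the participant's own stakeholder group, or each stakeholder group in turn.

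Participants do report "years of experience, field of interest, working country and current position, to help to define the composition of the panel". No use of field of interest in the consensus analysis is described.

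The three arm-specific sets go to the consensus meeting. Its stated purposes are to settle on one set, to discuss how outcomes should be measured, and to plan dissemination.

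**The concern.** The Background defines a COS as the minimum to be measured and reported in all trials of a condition. Each outcome in this set therefore becomes an expectation for paediatric trials too, and each outcome left out does not. A percentage taken over adult and paediatric responses together can hide disagreement between the two, and the smaller group has the smaller influence on it.

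The comparison of the three arms would not reliably show this. Each arm pools the two populations in the same way and, being randomised, should have a broadly similar mix. The arms could agree while sharing the same blind spot, and in that case the Consensus meeting section says a single set goes forward. Feedback by stakeholder group does not isolate paediatric views either.

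At stake is whether the study can support its own statement that the set serves children. The error could run either way: an outcome proposed with little paediatric support, or one omitted despite strong paediatric support.

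**Working it through.** The article gives no error rate or panel mix for the consensus rule, so there is no figure of its own to reproduce. The check asks how far the pooled percentage can depart from the paediatric one.

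**Inputs from the article (Delphi Analysis section):** more than 70% of responses at 7 or greater; at most 15% below 3; all responses in the arm as denominator.

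**Assumption:** the paediatric share of responses in an arm, *s*, is not stated. Values from 10% to 30% are shown.

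**Formula.** Let *p* be the proportion of paediatric participants rating an outcome 7 or more, and *a* the proportion among everyone else. The pooled percentage is *s·p* + (1 − *s*)·*a*.

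- No paediatric support (*p* = 0): the 70% limit is met when *a* > 0.70/(1 − *s*).
- Half support (*p* = 0.5): it is met when *a* > (0.70 − 0.5*s*)/(1 − *s*).
- Full support (*p* = 1): it is still missed when *a* ≤ (0.70 − *s*)/(1 − *s*).

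| Paediatric share *s* | Met with *p* = 0 if *a* exceeds | Met with *p* = 0.5 if *a* exceeds | Missed with *p* = 1 if *a* is at or below |
|---|---|---|---|
| 10% | 0.70/0.90 = 77.8% | 0.65/0.90 = 72.2% | 0.60/0.90 = 66.7% |
| 15% | 0.70/0.85 = 82.4% | 0.625/0.85 = 73.5% | 0.55/0.85 = 64.7% |
| 20% | 0.70/0.80 = 87.5% | 0.60/0.80 = 75.0% | 0.50/0.80 = 62.5% |
| 30% | 0.70/0.70 = 100%, impossible | 0.55/0.70 = 78.6% | 0.40/0.70 = 57.1% |

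**The low-score limit.** If nobody else scores below 3, the fraction of paediatric participants who could do so without breaching 15% is 0.15/*s*, capped at 1. That is all of them when *s* is 15% or less, and 0.15/0.20 = 75% of them at 20%. This limit does not protect a small minority.

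**Two less extreme examples at *s* = 15%.**

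- *a* = 85%, *p* = 10%: 0.15 × 0.10 + 0.85 × 0.85 = 73.75%. The outcome meets the 70% limit with 10% paediatric support.
- *a* = 60%, *p* = 95%: 0.15 × 0.95 + 0.85 × 0.60 = 65.25%. The outcome fails with 95% paediatric support.

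**Precision of a paediatric percentage.** Suppose true paediatric support is 75%. With 20 paediatric respondents, an outcome misses the limit of more than 70% if 14 or fewer rate it 7 or more; the binomial probability is 0.38. With 30 respondents the cut is 21 or fewer and the probability is 0.33. These respondent numbers are assumptions too.

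**The case against.** One common set is a deliberate choice, and the article is consistent about it. Any minority in a pooled vote is exposed to the same arithmetic, and nothing in the article shows that adult and paediatric ratings differ. The questionnaire wording is not shown, so participants may be scoring for ventilation trials in general; that paediatric participants score with children in mind is an inference. Funders or industry representatives may have no adult or paediatric identity at all. A condensed article could also leave summaries by participant characteristic to a fuller document.

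Much of this stands, and it limits the point. A reader might infer that a single pooled percentage declares outcomes core for children on adult clinicians' votes. The article does not support that. There are three percentages per outcome, one per arm. They yield proposals, which the meeting turns into a final set. The other votes come from all seven stakeholder groups, not from adult clinicians alone. The passes with zero paediatric support are extreme cases, and at a 20% share with half support the bar for the rest moves only from 70% to 75%.

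It does not remove the point. The article itself fixes the decision rule and names both populations as the target, and the meeting purposes it lists include no adult/child check. It states no route back for an outcome that failed the threshold. Whether the two populations agree is an open question that the described steps would leave unanswered.

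**Conclusion.** The point holds as a worthwhile, inexpensive improvement. It is not a contradiction in the article, nor evidence that the resulting set would be wrong for children.

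The consensus rule combines adult and paediatric responses within each arm, and no step described before or at the meeting examines the paediatric ones separately. How much this matters depends on the unstated paediatric share and on whether ratings diverge. At shares of 10% to 20% the pooled result can differ from the paediatric one in both directions. From 30%, inclusion with no paediatric support is ruled out, but exclusion despite full paediatric support remains possible.

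**What to change.** The Study status section says the Delphi has not begun, so the following can be settled before round 1.

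1. Make sure the field-of-interest item has adult, paediatric, both and neither as response options. The article does not show the present options.
2. Keep the arm-specific rule as the primary rule.
3. In addition, tabulate the same two percentages, with denominators, for participants with adult interest and for those with paediatric interest, by arm and pooled over arms. Count those answering both in each table.
4. Bring any outcome that meets the rule in one population but not the other to the consensus meeting, for explicit discussion of whether it is core for both populations or for one only.

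Do not require an outcome to pass in both populations automatically. With a small paediatric group, a well-supported outcome would often miss 70% by chance, as the binomial figures show.

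The cost is a few extra tables and some meeting time. The paediatric percentages may be imprecise, and must be shown with their denominators so that they are not over-read.

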### Aims and research questions

The primary aim is to develop a COS for trials involving patients undergoing mechanical ventilation where an aim of the intervention is to modify time spent on mechanical ventilation. The secondary aims are to determine the most valid method of gaining consensus for a COS, and to evaluate the COS uptake 5 and 10 years after its publication.

Our research questions are:Which outcomes are ranked by stakeholders as critical for inclusion in the COS?How is the ranking process influenced by the method of stakeholder group feedback during Delphi rounds?Do Delphi panel participants rank the importance of outcomes differently depending on their knowledge of the other groups’ ranking?Does participation by investigators in the Delphi panel affect their subsequent use of the COS, compared with investigators who do not participate?

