### The Delphi questionnaire and rounds

The Delphi will be managed using a bespoke online e-management system maintained by the COMET Initiative. This system has previously been used in the Management of Otitis Media with Effusion in Cleft Palate (MOMENT) study developing a COS for trials investigating otitis media with effusion in children [14]. It has been modified for this project to accommodate data collection, randomisation process, web link to the relevant questionnaire and presentation of scoring within each round.

### Round 1

We will use the most frequently reported outcomes identified from our systematic review for the first Delphi round. Participants will be asked to score each outcome using the Grading of Recommendations Assessment, Development and Evaluations (GRADE) scale of 1–9, where 1 represents least important and 9 represents most important [15]. Participants will have the option to suggest additional outcomes for inclusion in the second round. We will list outcomes in alphabetical order to avoid potential weighting. Outcomes suggested during round 1 will be reviewed and coded by two research team members to ensure they represent new outcomes; where uncertainty exists, the advisory group will be consulted. Scores attributed to each outcome will be calculated as a percentage of the total responses for all scores. This will be summarised by stakeholder groups and all outcomes will be carried forward to round 2. A flowchart of the study is shown in Fig. 1.

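### The nested feedback trial is compared by three lists cut at 70%, with no effect measure or uncertainty, so feedback effects cannot be told from chance

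*Protocol article*

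**What the plan says.** All references are to the protocol article.

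- **Aims and research questions.** A secondary aim is to "determine the most valid method of gaining consensus for a COS". Question 2 asks how the feedback method influences ranking. Question 3 begins "Do Delphi panel participants rank the importance of outcomes differently depending on their knowledge of the other groups" and so concerns how individual panel members score.
- **Randomisation.** "After round 1, participants will be randomised to one of three groups that will determine the method of feedback they will receive". Group 1 sees pooled responses of the whole panel, group 2 sees those of its own stakeholder group only, and group 3 sees those of every stakeholder group separately. On strata: "Participants will be stratified by type of stakeholder to ensure equal representation in each study group".
- **Analysis (Delphi study).** "The final responses will be analysed for each of the three study groups". An outcome enters an arm's list if the responses show ">70% of responses rating the outcome at 7 or greater and not more than 15% of responses rating the outcome <3". The between-arm step is then "We will explore similarities and differences across the three COS generated by the different feedback methods". The same section says that no feedback method is a gold standard.
- **Consensus meeting.** The research team reviews how far the three lists agree. If they agree, one list goes to the meeting; if they vary, the meeting discusses this and settles on one.
- **Analysis (observational cohort study).** Here the article does name an outcome, a chi-square test and a 0.05 significance level.

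**The concern.** The randomised comparison is reduced to one in-or-out flag per outcome per arm. Such a flag fails in two directions. An outcome whose true support is near 70% will fall on different sides of the line in different arms by sampling error alone. A real shift that stays on one side of 70% leaves no trace.

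Questions 2 and 3 are about how people score once they have seen a given kind of feedback. A list comparison gives a coarse, unquantified answer to question 2 and says nothing about individual scoring for question 3. The secondary aim also asks for a verdict on validity, which the article itself says has no reference standard.

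The comparison is also used in conduct. Agreement or variance between the lists decides what the consensus meeting is asked to settle, and the Discussion expects the study to guide the design of future Delphi studies.

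**Working it through.** The article gives no sample size, power or significance level for the nested trial, so there is no figure to reproduce. The check asks how the stated comparison behaves when feedback has no effect, and when it has one.

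**Inputs from the article:** three arms; inclusion needs more than 70% of responses at 7 or above.

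**Assumptions:** 30, 60 or 100 final responders per arm (panel size is left as large as possible); 40 outcomes; true proportion *p* scoring 7 or more uniform over 0.40 to 0.95; the rule on scores below 3 left out.

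**Step 1: chance that one arm includes an outcome.** q(n, p) = P(X ≥ r), with X binomial(n, p) and r the smallest whole number above 0.70n. This gives r = 22, 43 and 71 for n = 30, 60 and 100.

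**Step 2: chance that the three arms disagree with no feedback effect.** D = 1 − q³ − (1 − q)³. For n = 60 and p = 0.70, q = 0.451, so D = 1 − 0.092 − 0.165 = 0.743.

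| True p | n = 30 | n = 60 | n = 100 |
|---|---|---|---|
| 0.70 | 74% | 74% | 75% |
| 0.75 | 66% | 52% | 38% |
| 0.80 | 34% | 12% | 3% |

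At the cut-off itself, a larger panel does not help. Away from it, disagreement falls as arms grow.

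**Step 3: expected number of discordant outcomes.** Averaging D over p from 0.40 to 0.95 gives 0.247, 0.178 and 0.139. Multiplied by 40, that is 9.9 (n = 30), 7.1 (n = 60) and 5.6 (n = 100). Correlation between one participant's scores does not change these means, though it would make identical lists more likely than under independence.

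**Step 4: a real difference that the lists hide.** Let two arms have true proportions 0.75 and 0.90. The chance that both include the outcome is q(n, 0.75) × q(n, 0.90):

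- n = 30: 0.674 × 0.998 = 0.67
- n = 60: 0.775 × 1.000 = 0.78
- n = 100: 0.850 × 1.000 = 0.85

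The larger the arms, the more often this 15-point difference goes unseen.

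**Step 5: what a score comparison offers.** Assume a 1-point difference, SD 2 and two-sided 0.05. Adjusting for a round-1 score with correlation ρ multiplies the residual variance by 1 − ρ², a cut of 25% at ρ = 0.5 and 49% at ρ = 0.7.

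| n per arm | Power, unadjusted | ρ = 0.5 | ρ = 0.7 |
|---|---|---|---|
| 30 | 49% | 61% | 77% |
| 50 | 70% | 82% | 94% |

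The adjustment is a gain in precision. Randomisation already makes the unadjusted comparison of final scores valid.

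**The case against.** This is a condensed article whose analysis plan is not shown, and covariate adjustment, stratum terms and intervals are commonly left to such a plan. A reader might infer that the trial will ignore round-1 scores and the stratification, or that lists are all that will ever be compared. The article does not support that. It says only of the round-1 percentages that "This will be summarised by stakeholder groups and all outcomes will be carried forward to round 2"; it rules out no further use of them or of the strata, and the statement that final responses are analysed by arm could cover summaries of the score distribution. A reader might also infer that questions 2 and 3 cannot be answered without change from round 1. That is wrong too, because allocation follows round 1 and final scores can be compared directly.

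The article also promises to explore rather than test, and nowhere says that list differences will be taken as proof of a feedback effect. The magnitudes rest on assumed sizes and spreads, and the 74% applies to an outcome exactly at the cut-off.

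These limits are accepted. What remains is the comparison that the article does state, in both the Analysis and Consensus meeting sections. It is poorly suited to the questions asked, and it is less specified than the cohort analysis in the same article.

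**Conclusion.** The point holds in this form: the stated between-arm comparison is a descriptive look at three thresholded lists, with no effect measure or uncertainty. It answers question 2 crudely, leaves question 3 unaddressed at participant level, and cannot separate feedback effects from chance. Under the assumptions above, roughly 10 down to 6 of 40 outcomes would differ by chance alone at 30 to 100 per arm, while a true 75% versus 90% difference would be hidden in 67% to 85% of studies. The stronger conclusion that the nested trial cannot answer its questions is not supported: the design is sound and the needed data are collected. The fault is in the stated analysis.

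Separately, the aim of identifying the most valid method conflicts with the article's own statements, under Analysis and Consensus meeting, that no gold standard exists.

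Severity: should-fix. The primary aim of developing the core outcome set does not depend on this comparison.

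**What to change.** 1. Make the between-arm analysis a comparison of participants' final scores, and of 7 or above versus below. Report arm differences with 95% confidence intervals and allow for repeated outcomes within a participant.
2. Use group 3 versus group 2 for research question 3, since they differ in whether other stakeholder groups' responses are seen.
3. For precision, adjust for stakeholder stratum and for the participant's own round-1 score. The latter applies only to outcomes scored in round 1; those suggested in that round and added later have no baseline.
4. Keep the list comparison as descriptive. Show the number of discordant outcomes beside the number expected by chance, and judge agreement between lists in that light before the consensus meeting.
5. Reword the secondary aim to comparing the effect of the feedback methods on scoring and on agreement.

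Cost: revised wording and modest extra analysis. The scores and strata are already collected, and the article says the Delphi study has not begun. The claim to find the most valid method is given up.
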